**5. RESEARCH METHODOLOGY**

**5.1 STUDY DESIGN AND METHODOLOGY**

Randomized Double Blind, Placebo Controlled Study

Study type: Interventional

This is a randomized, double-blind, placebo-controlled clinical trial. Recruitment of Parkinson disease patients with constipation will be done from the neurology clinic HUKM. Patients are considered eligible if they meet the Rome III criteria for functional constipation^33^ (2 or more criteria as listed in the box below in at least 25% occasion for the last 3 months) and will be provided written informed consent. Standard therapy for constipation is Syrup lactulose (osmotic agents) which promote intestinal motility and secretion. The recommended dose of lactulose for adults is 15 to 30 mL once or twice daily. The use of syrup lactulose is not forbidden and patient will be advised to take syrup lactulose as per needed. Fecal occult blood testing will be used to screen for colorectal malignancy in all eligible patients prior to intervention as positive test patients will not be included in the study. After written informed consent given, patients’ demographic data were collected.

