|  | **6. HOSPITAL PROFILE/DEMOGRAPHIC**  **7. STUDY PERIOD**  June 2018 – June 2019  **8. SUBJECTS**  **8.1 TARGET POPULATION**  Patients with Parkinson disease attending the neurology outpatients clinic who fulfil inclusion and exclusion criteria  **9. SAMPLING**  **9.1 INCLUSION CRITERIA**   1. Idiopathic PD diagnosed using UK PD Society Brain Bank Criteria 2. Diagnosis of constipation according to Rome III Functional Constipation Criteria 3. Written informed consent   **ROME III Diagnostic Criteria : Functional Constipation**   \| Functional Constipation \| \| --- \| \| Must include 2 or more of the following:  Straining *  Lumpy or hard stools*  Sensation of incomplete evacuation*  Sensation of anorectal obstruction/blockage*  Manual manoeuvres to facilitate defecation(digital evacuation, support of pelvic floor)*  <3 defecation per week*  ***≥25% of defecations**  Loose stool rarely present without use of laxatives  Insufficient criteria for IBS \|   Based on Longstreth GF et al.Gastroenterology 2006 ;130:1480-1491  **9.2 EXCLUSION CRITERIA**   1. Secondary Parkinsonism 2. Previous history of small and large bowel disease 3. Previous extensive gastrointestinal tract surgery 4. Positive stool occult blood in the last 1 month 5. Use of probiotics or antibiotics in 2 weeks before baseline visit 6. Underlying Dementia 7. Hypothyroidism 8. Diagnosed with major depression and on antidepressant 9. Lactose intolerance   10. Type 1 and Type 2 DM  **10. DATA COLLECTION**  **10.1 METHOD OF DATA COLLECTION**  Patients with idiopathic PD attending the neurology outpatients’ clinic will be invited to participate in the study. All subjects will be screen for constipation by using Rome III Criteria – Constipation Module. Written informed consent will be obtained from all subjects after screening inclusion and exclusion criteria. Baseline demographic data will be recorded into a structured questionnaire.  Screening assessment :  1) Constipation screening using Rome III Criteria – Constipation Module  2) Fecal occult blood testing - negative test will be included in the study  The eligible subjects will be assess on the first visit as below :  1) Constipation symptoms by using Garrigues Constipation module (GQ)  2) Quality of life by using PDQ39 Questionnaire (self-administered malay version )  3) Parkinson Disease severity by using MDS-UPDRS  4)Non motor symptoms of PD by using NMS scale  (All the above questionnaires are validated)  Subsequently, subjects will be instructed to consume 4 red carmine capsule(food colourant) and once the stool turn red in colour, Gatrointestinal Transit Time(GTT) will be measured and recorded. Subjects will then receive a 3g sachet of either probiotics (containing multistrains of lactobacillus and Bifidobacterium 30 Colony Forming Unit) or placebo twice-daily for a duration of 8 weeks. Once consumption completed, subjects need to consume again another 4 red carmine capsule and GTT will be measured and recorded again. Final assessment will be done once subjects completed all the probiotics or placebo given(week 8) and subjects need to be assess again on constipation symptoms, non-motor symptoms, quality of life and disease severity same as done at baseline using the same questionnaire.  **10.2 STUDY PROTOCOL**  Randomization  All patients who fulfill inclusion and exclusion criteria will be stratified based on age, sex and background social economics. Patients who are enrolled will be randomized into two treatment groups which a probiotics group who will receive probiotics (containing multistrains of lactobacillus and Bifidobacterium 30 Colony Forming Unit) or placebo using blocks randomization method, in blocks of 4. Patients and investigator will remain blinded to the treatment protocol.  Following randomization, patients will receive their assigned treatment from the pharmacy department, Hospital Canselor Tuanku Muhriz, PPUKM  Treatment  Active treatment group will receive a 3 gram sachet of probiotics containing multistrains of lactobacillus and Bifidobacterium 30 Colony Forming Unit x 10^9^ to be taken twice daily for 8 weeks.  Composition of probiotics:   \| Lactobacillus acidophilus \| 107mg \| \| --- \| --- \| \| Lactobacillus casei \| 107mg \| \| Lactobacillus lactis \| 107mg \| \| Bifidobacterium bifidum \| 107mg \| \| Bifidobacterium infantis \| 107mg \| \| Bifidobacterium longum \| 107mg \|   Placebo group will receive a 3g sachet of substance (powder form) that has no therapeutic effect to be taken twice daily for 8 weeks.  All test products will be concealed in sealed envelopes, to ensure blindedness  **10.3 STUDY ASSESSMENT**  All patients will be assessed at baseline and week 8 for improvement in constipation symptoms using the Garrigues Constipation Questionnaire^35^, Quality of Life by using self- administered PDQ39 questionnaire (malay version)^36^, disease severity by using MDS-UPDRS and non-motor symptoms by using NMS scale . The Gastrointestinal transit time will be assessed at baseline and week 8 using red carmine capsule. Compliance to treatment, side effects and clinical assessments will be performed by a blinded assessor at baseline and week 8 for both groups.  **Gastrointestinal Transit Time Protocol**  Following randomization, subjects will be instructed to ingest 4 red carmine capsule after last bowel opening. Red carmine capsule is a food colorant and non-toxic to body which is used to measure GTT. The time of ingestion will be recorded. GTT is measured from the time of red carmine capsules consumption and first appearance of red colored stool. The duration from time of ingestion and appearance of red colored stool (Gastrointestinal transit time) will be recorded by patient at baseline, and week 8. The use of laxatives is not forbidden, but patients are required to use as per needed. GTT was measured during pre and end treatment in both groups.  **Constipation-Related Symptom Assessment**  Constipation related symptoms will be assessed using the Garrigues Constipation Questionnaire (GQ)^35^ which is a 21-item that was developed to define the presence of chronic constipation. Only 13 of the 21 items are related to bowel habits. The Rome 111 criteria were used to define constipation. The items are scored using two different four-point Likert scales. The first consisted of ‘never’, ‘sometimes’ (25% of the time) and ‘always’. The second consisted of ‘never’, ‘fewer than once a week’, ‘one or more times a week’ and ‘every day’. Total and cut off scores were not reported.  **Quality Of Life Assessment**  Baseline Quality of life patients will be assess using self-administered PDQ-39^36^ Questionnaire(Malay version) and end of intervention, subject will be assessed again using the same questionnaire. PDQ-39 questionnaire contains 39 items with each item was rated by the patients using one of five categories, from 0 (never) to 4 (always). PDQ-39 summary index (PDQSI) is calculated by dividing the sum of the total raw score by the maximum possible score (156 or 152 points, depending on the patient’s marriage status) and multiplying by 100. In this study, we will use PDQSI as a standardized index for representing PD patients’ life quality.  **Non Motor symptoms (NMS) assessment**  Severity of Non Motor symptoms of each individual will be assess using NMSS Questionnaire. Frequency and severity of each NMS are taken into account. Final total score of disability (0=no disability; 360=maximal disability).  **DDisease severity assessment**  Parkinson Disease severity assessment will be assess using MDS-UPDRS questionnaire. MDS UPDRS has four parts which include nonmotor experiences of daily living (13 items), motor experiences of daily living (13 items), motor examination (18 items), and motor complications (six items). Each subscale now has 0-4 ratings, where 0 = normal, 1 = slight, 2 = mild, 3 = moderate, and 4 = severe.  10.4 **VALIDITY OF TOOLS**  NMS and MDS-UPDRS are public domain questionnaire  Validated score : PDQ 39 (malay version)- permission obtained from author  Garrigues Constipation Questionnaire- awaiting permission from author  **11. STASTICAL ANALYSIS**  Statistical Package for the Social Sciences (SPSS) Software version 2 will be used for statistical analysis. Age, height, weight, body mass index (BMI) and gender were compared between the groups by Student’s t-test and the chi-squared test. General Linear Model will be used to compare intestinal transit time in probiotics and placebo groups before and after 8 weeks of intervention. Pre- and post-probiotics consumption data on clinical evaluation of constipation that will be obtained from all the questionnaires namely Rome III criteria, PDQ-39 Questionnaire and Garrigues Constipation Questionnaire will be analysed using Mc Nemar Test. Independent t-test will be used to compare the differences of intestinal transit time in both groups. Pearson correlation and Simple linear regression analysis will be utilized to explore the relationship and effect between two numerical variables. A p-value <0.05 will be considered as statistically significant.  **11.1 SAMPLE SIZE CALCULATION**  The sample size is being calculated based formula comparing between two proportions. Sample size calculation was performed according to a study by Sakai et al^32^ based on value reported on changes in percentage of bowel movements and complete bowel movements after 3 weeks of probiotics treatment where there was a significant decreased from 73.7% to 36.8%,  Formula for sample size comparing two proportions:  [figure not shown]  Sample size was estimated as follows :  p1 = 0.737  p2 = 0.368  zα = 1.96  zβ = 0.84  n = 0.737 (1 – 0.737) + 0.368 (1 – 0.368 ) X (1.96 + 0.84) ^2^  (0.737 – 0.368) ^2^  n = 0.193831 + 0.232576 X 7.84  0.136161  n = 25 per group  The number of samples per group is further added 20% to compensate for non-response and lost to follow up. The final samples required for each group is 30 patients. |

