**Screening :**

**Rome III Criteria – Constipation Module**

**Negative Fecal occult blood**

**Fulfil inclusion/ exclusion criteria**

2^ND^ VISIT- WEEK 8

Constipation assessment with GQ

Quality of life assessment with PDQ39

Disease severity assessment with MD S- UPDRS

Non motor symptoms assessment with NMS

Questionnaires

Determination GTT

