**Rome III Criteria – Constipation Module^1^ (CONSTIPATION SCREENING FORM)**

| **Q1.** In the last 3 months, how often did you have discomfort or pain anywhere in your abdomen? | | |  | **Q11.** In the last 3 months, how often did you strain during bowel movements? | | |
| --- | --- | --- | --- | --- | --- | --- |
|  | Never |  |  |  | Never or rarely |  |
|  | Less than one day a month |  |  |  | Sometimes |  |
|  | One day a month |  |  |  | Often |  |
|  | Two to three days a month |  |  |  | Most of the time |  |
|  | One day a week |  |  |  | Always |  |
|  | More than one day a week |  |  |  |  |  |
|  | Every day |  |  |  |  |  |
|  | | |  |  |  |  |
| **Q2.** For women: Did this discomfort or pain occur only during your menstrual bleeding and not at other times? | | |  | **Q12.** In the last 3 months, how often did you have a feeling of incomplete emptying after the bowel movements? | | |
|  | No |  |  |  | Never or rarely |  |
|  | Yes |  |  |  | Sometimes |  |
|  | Does not apply because I have had the change in life (menopause) or I am a male |  |  |  | Often |  |
|  |  |  |  |  | Most of the time |  |
|  |  |  |  |  | Always |  |
|  | | |  |  |  |  |

| **Q3.** Have you had this discomfort or pain 6 months or longer? | | | |  | **Q13.** In the last 3 months, how often did you have a sensation that the stool could not be passed, (i.e. , blocked), when having a bowel movement? | | |
| --- | --- | --- | --- | --- | --- | --- | --- |
|  | No | |  |  |  | Never or rarely |  |
|  | Yes | |  |  |  | Sometimes |  |
|  |  | |  |  |  | Often |  |
|  |  | |  |  |  | Most of the time |  |
|  |  | |  |  |  | Always |  |
|  | | | |  |  |  |  |
| **Q4.** How often did this discomfort or pain get better or stop after you had a bowel movement? | | | |  | **Q14.** In the last 3 months, how often did you press on or around your bottom or remove stool in order to complete a bowel movement? | | |
|  | Never or rarely | |  |  |  | Never or rarely |  |
|  | Sometimes | |  |  |  | Sometimes |  |
|  | Often | |  |  |  | Often |  |
|  | Most of the time | |  |  |  | Most of the time |  |
|  | Always | |  |  |  | Always |  |
|  | | | |  |  |  |  |
| **Q5.** When this discomfort or pain started, did you have more frequent bowel movements? | | | |  | **Q15.** In the last 3 months, how often did you have difficulty relaxing or letting go to allow the stool to come out during a bowel movement? | | |
|  | Never or rarely | |  |  |  | Never or rarely |  |

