| **Q7.** Indicate which drugs you are taking | | | | | | |  | | **Q17.** Do you need to use suppositories to have bowel movements? | | |
|  | | Non steroidal anti inflammatory (NSAIDs) | | | | |  | |  | Never |  |
|  | | Anxiolytics | | | | |  | |  | Fewer than once a week |  |
|  | | Calcium channel antagonist | | | | |  | |  | One or more times a week |  |
|  | | Female hormone based drugs | | | | |  | |  | Every day |  |
|  | | |  |  | |  | |  |  |  |  |
|  | | | | | | |  | |  |  |  |
| **Q8.** Have you felt constipated? | | | | | | |  | | **Q18.** Do you need to use enemas to have bowel movements? | |  |
|  | | Yes | | | | |  | |  | Never |  |
|  | | No | | | | |  | |  | Fewer than once a week |  |
|  | |  | | | | |  | |  | One or more times a week |  |
|  | |  | | | | |  | |  | Every day |  |
|  | |  | | | | |  | |  |  |  |
| **Q9.** Do you strain during a bowel movement? | | | | | | |  | | **Q19.** Have you visited a doctor because of constipation? | |  |
|  | | Never | | | | |  | |  | Yes |  |
|  | | Sometimes (less than 25% of time) | | | | |  | |  | No |  |
|  | | Often (more than 25% of time) | | | | |  | |  |  |  |
|  | | Always | | | | |  | |  | |  |
|  | |  | | | | |  | |  |  |  |
| **Q10.** Do you feel an incomplete emptying sensation after a bowel movement? | | | | | | |  | | **Q20.** Have you presented with abdominal pain more than six times this past year? | |  |
|  | | Never | | | | |  | |  | Yes |  |
|  | | Sometimes (less than 25% of time) | | | | |  | |  | No |  |
|  | | Often (more than 25% of time) | | | | |  | |  |  |  |
|  | | Always | | | | |  | |  |  |  |
|  | |  | | | | |  | |  | |  |
|  | |  | | | | |  | | **Q21.** Have you presented with loose or watery stools? | |  |
|  | |  | | | | |  | |  | Yes |  |
|  | |  | | | | |  | |  | No |  |
|  | |  | | | | |  | |  |  |  |

^1^Garrigues et al *Am J Epidemiol* 2004

PDQ-39 (MALAY)

| Name:  MRN:  (Sticker) |  | Day 0 |  |  |
| --- | --- | --- | --- | --- |
|  |  | Date | / / 2018 | |

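### Section 11 tests Rome III status before and after treatment with McNemar, although every patient must be Rome III positive at entry and no week-8 Rome III assessment is scheduled

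*Combined protocol and SAP*

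**What the plan says.** Entry: section 5.1 states "Patients are considered eligible if they meet the Rome III criteria for functional constipation", with the threshold "2 or more criteria as listed in the box below in at least 25% occasion for the last 3 months". Inclusion criterion 2 in section 9.1 repeats it: "Diagnosis of constipation according to Rome III Functional Constipation Criteria".

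Analysis: section 11 lists "Pre- and post-probiotics consumption data on clinical evaluation of constipation that will be obtained from all the questionnaires namely Rome III criteria" and continues "PDQ-39 Questionnaire and Garrigues Constipation Questionnaire will be analysed using Mc Nemar Test". It names no between-arm test for these data, although the first primary objective (section 4.1) is an effect on constipation relative to placebo.

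Tool: the bowel items of the appended Rome III Module carry a three-month window, for example "In the last 3 months, how often did you strain during bowel movements".

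Schedule: section 10.1 uses Rome III at screening. Section 10.3 lists GQ, PDQ-39, MDS-UPDRS and the NMS scale at baseline and week 8. The flow chart's week-8 visit shows "Constipation assessment with GQ" and does not list Rome III.

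**The concern.** A McNemar test sets patients who improved against patients who worsened. When a positive status is the condition for entry, nobody can worsen on overall status, so every change counts as improvement. Regression to the mean after selection, placebo response and the as-needed lactulose that section 5.1 permits could each move enough patients to make an arm significant without any probiotic effect. A significant probiotic arm beside a non-significant placebo arm could then be read as efficacy, although the two arms were never compared.

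The recall window is a second and opposite problem. A three-month question asked after eight weeks of treatment mixes treated and untreated weeks, which favours persistence of a positive status and can hide a real benefit.

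Third, the analysis section names a post-treatment measure that the visit schedule does not list.

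**Working it through.** **Inputs**
- Rome III status at entry: 100% positive (sections 5.1 and 9.1).
- Arm size: 25 evaluable, 30 recruited (section 11.1). Significance level 0.05 (section 11).
- Treatment 8 weeks = 56 days, with the final assessment at week 8 (sections 10.1 to 10.3).
- Module recall: 3 months, taken as 91 days (range 90 to 92).
- Reversion rate to Rome III negative on placebo: not in the documents. Assumed range 10% to 30%.

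**1. The plan's own arm size.** (0.193831 + 0.232576) × 7.84 / 0.136161 = 24.55, rounded to 25; 25 × 1.2 = 30. The stated figures reproduce. They are used here only as the arm size.

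**2. The test when nobody can worsen.** With k patients turning negative and 0 turning positive, exact two-sided p = 2 × 0.5^k.
- k = 5: p = 0.0625
- k = 6: p = 0.031

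Six of 25 (24%) is enough. The plan does not say which version of McNemar is meant. The continuity-corrected test also needs 6 (p = 0.041); the uncorrected one needs only 4 (p = 0.046).

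**3. Chance that one arm is significant.** This is P(X ≥ 6), with X binomial(n, q):

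| Assumed reversion rate q | n = 25 | n = 30 |
|---|---|---|
| 10% | 3% | 7% |
| 15% | 16% | 29% |
| 20% | 38% | 57% |
| 25% | 62% | 80% |
| 30% | 81% | 92% |

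Suppose both arms revert at 20% with 25 patients each, so there is no treatment effect. Exactly one arm is significant with probability 2 × 0.383 × 0.617 = 47%, and both with probability 0.383² = 15%. For contrast, a Fisher exact comparison of week-8 status between the arms has a type I error of 0.9%, 2.2% and 2.3% at reversion rates of 10%, 20% and 30% (n = 25).

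**4. Recall overlap, if the Module is used at week 8.** 91 − 56 = 35 days, and 35/91 = 38% (34/90 = 38%; 36/92 = 39%). Assume evenly spread bowel movements, and let f0 and f1 be a symptom's frequency before and during treatment. The three-month average is (35/91)·f0 + (56/91)·f1, and the criterion clears only when this falls below 25%.
- f0 = 50%: f1 must fall to (0.25 − 0.385 × 0.50)/0.615, about 9%.
- f1 = 0 (complete resolution): the average stays at or above 25% whenever f0 is at least 0.25/0.385 = 65%.

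**5. Which tool supplies the week-8 status.** Two readings are possible:
- *The Module.* It appears only as a screening form, so section 11 asks for data that no week-8 visit lists.
- *The GQ.* The GQ paragraph of section 10.3 says that Rome III was used to define constipation. GQ Q9 to Q13 cover straining, incomplete emptying, hard stools, blockage and manual manoeuvres, with response options split at 25%, and Q15 asks weekly frequency. These items have no three-month window, and the GQ is scheduled at both visits. Section 5.1, however, defines Rome III positivity over three months.

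The text does not settle which is meant.

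**6. Two GQ items in the same pre/post analysis.** Q19 (a doctor visit because of constipation) has no time limit. Q20 asks "Have you presented with abdominal pain more than six times this past year"; at week 8, 52 − 8 = 44 of its 52 weeks (85%) precede treatment.

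**The case against.** The strongest reply has four parts.

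- *The test need not be significant.* This stands. A reader might infer that Rome III will show improvement in any arm, or that the test is bound to favour it. The documents support only that overall status cannot worsen. Five or fewer reverters of 25 is non-significant by the exact test, and at a 10% reversion rate a significant placebo arm is rare (3%).
- *The two defects oppose each other.* This also stands. If the Module's window makes reversion harder, the higher rates in the table become less plausible. But nothing makes the two effects offset, and neither leaves a valid estimate of probiotic against placebo.
- *Rome III may be scored from the GQ.* This is possible. The schedule gap would then close and the recall overlap would lessen. Re-scoring at baseline with a different tool could leave a few patients negative, so the worsening cell would be small rather than strictly zero. Selection on constipation and the missing between-arm comparison would remain.
- *The false signal comes from within-arm testing in general.* This is largely right. Universal positivity at baseline does no harm once randomised arms are compared at week 8. It does make the within-arm test particularly uninformative here.

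A reader might also infer that GQ Q20 cannot change in eight weeks. It can, because old episodes drop out of the rolling year. It is insensitive rather than fixed.

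**Conclusion.** The point holds. As written, the Rome III analysis in section 11 cannot answer the placebo-controlled objective in section 4.1, whichever tool supplies the status. For 25 per arm, the chance of a significant placebo arm runs from 3% to 81% over assumed reversion rates of 10% to 30%. That width reflects a rate the documents do not supply.

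The one-direction argument assumes that overall Rome III status is analysed. Section 11 does not say so, and single items need not all be positive at baseline. The 38% overlap assumes that the appended Module is used unchanged at week 8; that contamination is conditional, not established. The mismatch between the analysis and the schedule is firm if the Module is meant and becomes an ambiguity if the GQ is meant; either way the text needs correcting. Transit time has its own between-group analysis and is not affected.

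**What to change.** Preferred: use Rome III for eligibility only and delete it from the pre/post McNemar analysis in section 11. This costs a wording change; symptom evaluation then rests on the GQ, which is already scheduled at both visits.

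Alternative, if a week-8 Rome III outcome is wanted: add it to sections 10.1 and 10.3 and to the flow chart's week-8 visit, state which tool and which overall-status definition apply, use a recall period inside the eight treatment weeks, and compare the week-8 proportion between randomised arms. The cost is one more form at week 8 and a recall wording that departs from the appended form. Changing only the test would leave the recall overlap in place.

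Under either option, reconcile sections 10.1, 10.3 and 11 and the flow chart, and say whether the Rome III remark in the GQ paragraph means that status is derived from GQ items. Leave GQ Q19 and Q20 out of any eight-week change analysis. Leave the GQ recall wording as it is: the protocol describes the instrument as validated and is still awaiting permission to use it, so altering it would create a new problem.

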**4. OBJECTIVE**

**4.1 PRIMARY OBJECTIVE**

- To determine the effects of probiotics (multistrains of Lactobacillus and Bifidobacterium ) on constipation among Parkinson disease patients compared to placebo
- To determine the effects of probiotics on Gastrointestinal Transit Time (GTT) compared to placebo

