**4.2 SECONDARY OBJECTIVE**

- To determine the effects of probiotics on overall quality of life compared to placebo
- To determine the effects of probiotics on disease severity and non-motor symptoms score.

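### Constipation and quality of life are analysed only by a before/after McNemar test, so the plan never compares probiotic with placebo on its first primary objective

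*Combined protocol and SAP*

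**What the plan says.** The trial is randomised, double-blind and placebo-controlled (section 5.1). Section 4.1 sets two primary objectives: the effect of probiotics "on constipation among Parkinson disease patients compared to placebo", and "To determine the effects of probiotics on Gastrointestinal Transit Time (GTT) compared to placebo". The first objective in section 4.2 is "To determine the effects of probiotics on overall quality of life compared to placebo".

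Section 11 describes the constipation and quality-of-life data as "Pre- and post-probiotics consumption data on clinical evaluation of constipation", drawn from the Rome III, PDQ-39 and Garrigues questionnaires, and says that they "will be analysed using Mc Nemar Test". For transit time it says "General Linear Model will be used to compare intestinal transit time in probiotics and placebo groups before and after 8 weeks of intervention", and adds an independent t-test.

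On scales, section 10.3 defines the PDQ-39 summary index as raw score over maximum score, times 100, and states "In this study, we will use PDQSI as a standardized index". It gives no cut-off for the index. It describes the Garrigues items as four-point scales and notes that no total or cut-off score was reported. The form in the appendix also has yes/no items and a weekly count of bowel movements.

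**The concern.** An objective worded against placebo needs a test that contains the arm. McNemar asks only whether the proportion with a state changed between two visits in the same patients. Every patient enters with constipation, and as-needed lactulose is allowed in both arms. Regression to the mean, placebo response and laxative use could therefore each produce improvement without any probiotic effect. A significant before/after change in the probiotic arm would not separate these from the product. If the plan is followed as written, the first primary objective and the quality-of-life objective go unanswered, although the randomised data needed to answer the quality-of-life objective, and constipation through the Garrigues items, will have been collected.

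There is also a mismatch of data type. McNemar needs a paired yes/no state, and the plan defines none for the PDQSI or for the Garrigues questionnaire.

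**Working it through.** **1. Which analyses in section 11 contain the arm?**

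| Analysis named | Applied to | Compares arms? |
|---|---|---|
| t-test, chi-squared | Age, height, weight, BMI, gender | Yes, baseline only |
| General Linear Model | Transit time | Yes |
| Independent t-test | Transit time | Yes |
| McNemar | Rome III, PDQ-39, Garrigues | No |
| Pearson correlation, simple regression | Any two numerical variables | Not tied to arm or outcome |

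No row compares arms on constipation or quality of life.

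**2. The sample size presumes a between-arm comparison.** Section 11.1 uses the formula for two independent proportions:

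n = [0.737(0.263) + 0.368(0.632)] × (1.96 + 0.84)² / (0.737 − 0.368)² = (0.193831 + 0.232576) × 7.84 / 0.136161 = 24.55, rounded up to 25; 25 × 1.2 = 30.

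The stated 25 and 30 per group reproduce. No efficacy outcome in section 11 receives the test that this formula sizes.

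**3. Data type.**
- Rome III status: yes/no, so McNemar fits its form.
- PDQSI: 0-100 index with no cut-off, so McNemar does not fit.
- Garrigues: ordinal, yes/no or count, with no total or cut-off, so there is no defined binary state for the questionnaire.

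**4. How often is McNemar significant when the probiotic does nothing?** The inputs are 25 evaluable per arm and 73.7% affected at baseline (both from section 11.1), and the exact two-sided test at 0.05. Assumed, because the documents give no placebo course: 10% of unaffected patients worsen, and the same fraction *i* of affected patients improve in both arms. Per patient, P(improve) = 0.737*i* and P(worsen) = 0.263 × 0.10 = 0.0263. Exact enumeration over these gives *s*, the chance that one arm's test is significant. The arms are independent with equal *s*, so the chance that the probiotic arm is significant and the placebo arm is not is *s*(1 − *s*), which cannot exceed 25%.

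| *i*, both arms | *s* | *s*(1 − *s*) |
|---|---|---|
| 10% | 0.5% | 0.5% |
| 20% | 9% | 8% |
| 30% | 32% | 22% |
| 40% | 59% | 24% |
| 50% | 79% | 17% |
| 60% | 91% | 8% |

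**5. Rome III status.** Eligibility makes everyone positive at entry, so change can go only one way. With *k* patients resolved and none worsened, the exact p-value is 2 × 0.5^k: 0.0625 at *k* = 5 and 0.031 at *k* = 6. Six resolutions therefore suffice. P(at least 6 resolve), with the same assumed resolution rate in both arms:

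| Resolution, both arms | n = 25 | n = 30 |
|---|---|---|
| 10% | 3% | 7% |
| 20% | 38% | 57% |
| 30% | 81% | 92% |
| 40% | 97% | 99% |

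**The case against.** The best defence has four parts.

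- **Transit time is compared between arms.** This stands. A reader might infer that the trial has no randomised primary comparison at all; sections 4.1 and 11 do not support that. The gap is in the first primary objective and in quality of life.
- **The plan states no rule of claiming benefit when one arm is significant and the other is not.** This also stands. It is tempting to quote a false-positive rate of about 25%, but that is the ceiling of *s*(1 − *s*), reached only for certain assumed courses and under a decision rule that the plan does not contain. At 10% improvement the figure is 0.5%. Read literally, the sentence tests the probiotic arm alone, and the relevant column is then *s*. The wording may equally be loose and mean McNemar in each arm; the difference between arms would still go untested.
- **McNemar is not wrong for every instrument.** Correct: it suits the binary form of Rome III status. The data-type fault is confined to the PDQSI and Garrigues.
- **The 73.7% is not clearly a baseline for this trial's endpoint.** Section 11.1 attributes it to bowel movements, while the literature review links the cited study to hard or lumpy stools. It serves here as the plan's own working figure and no more.

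None of this supplies a between-arm test for constipation or quality of life. The absence of any named test for MDS-UPDRS and the non-motor score is a separate omission; that objective is not worded against placebo.

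**Conclusion.** The point holds and must be fixed. Section 11 as written cannot answer the first primary objective or the quality-of-life objective, and this follows from the text without any assumption.

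The size does rest on assumptions about the course under placebo. With 25 per arm and 10-60% improvement common to both arms, the probiotic arm's test is significant 0.5-91% of the time with no treatment effect. An informal contrast of the two arms' p-values, which the plan does not propose, would favour the probiotic about 0.5-24% of the time. For Rome III status, 20% resolution in both arms gives a significant test 38% (n = 25) or 57% (n = 30) of the time. The documents cannot narrow these ranges.

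**What to change.** Replace the McNemar sentence in section 11 as follows.

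1. **Name one primary week-8 constipation endpoint from data already collected.** One example is Garrigues Q11 (hard stools), split at the form's own 25% boundary: often or always against never or sometimes. If Rome III status is preferred, state that the module is repeated at week 8; sections 10.1 and 12 list it only at screening.
2. **Compare probiotic with placebo on that endpoint** by chi-squared or Fisher's test, or by logistic regression adjusted for the baseline value. Report the risk difference with 95% CI. Baseline adjustment is not possible for Rome III status, because every patient is positive at entry.
3. **Compare PDQSI between arms** by ANCOVA of the week-8 score on arm and baseline score. Use the same model for the non-motor score and MDS-UPDRS.
4. **Treat the other Garrigues items as secondary**, with a between-arm ordinal comparison and no confirmatory claim.
5. **Report within-arm changes descriptively**, without p-values.

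The cost is one endpoint definition and a little more analysis. No new data are needed for a Garrigues endpoint; Rome III status would add one short questionnaire at the existing week-8 visit.
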